## Abstract

**Background:**

New technologies could facilitate changes in lifestyle and improve public health. However, no large randomized, controlled studies providing scientific evidence of the benefits of their use have been made. The aims of this study are to develop and validate a smartphone application, and to evaluate the effect of adding this tool to a standardized intervention designed to improve adherence to the Mediterranean diet and to physical activity. An evaluation is also made of the effect of modifying habits upon vascular structure and function, and therefore on arterial aging.

**Methods/Design:**

A randomized, double-blind, multicenter, parallel group clinical trial will be carried out. A total of 1215 subjects under 70 years of age from the EVIDENT trial will be included. Counseling common to both groups (control and intervention) will be provided on adaptation to the Mediterranean diet and on physical activity. The intervention group moreover will receive training on the use of a smartphone application designed to promote a healthy diet and increased physical activity, and will use the application for three months. The main study endpoints will be the changes in physical activity, assessed by accelerometer and the 7-day Physical Activity Recall (PAR) interview, and adaptation to the Mediterranean diet, as evaluated by an adherence questionnaire and a food frequency questionnaire (FFQ). Evaluation also will be made of vascular structure and function based on central arterial pressure, the radial augmentation index, pulse velocity, the cardio-ankle vascular index, and carotid intima-media thickness.

**Discussion:**

Confirmation that the new technologies are useful for promoting healthier lifestyles and that their effects are beneficial in terms of arterial aging will have important clinical implications, and may contribute to generalize their application in favor of improved population health.

**Trial registration:**

Clinical Trials.gov Identifier: NCT02016014

## Background

### Benefits of physical activity

There is abundant scientific evidence of the biological and psychological benefits of physical activity [1]. On the other hand, low cardiopulmonary fitness is associated with an increased risk of cardiovascular morbidity-mortality, while improved physical fitness is associated with a decrease in mortality risk [2]. The results of a metaanalysis on the influence of physical activity upon blood pressure indicate a mean reduction of 3.8 mmHg in systolic blood pressure (SBP) and 2.6 mmHg in diastolic blood pressure (DBP) [3]. Aerobic exercise could attenuate arterial hardening as observed in the Baltimore Longitudinal Study, in which male athletes had a lesser pulse wave velocity (PWV), augmentation index (AIx) and SBP than sedentary individuals [4]. Improvement in carotid artery elasticity has also been recorded in previously sedentary subjects who started a physical exercise program [5]. Aerobic exercise has been related to a decrease in atherosclerosis progression in humans [6]. The results of the first phase of the EVIDENT study [7] have demonstrated an association between physical exercise and improved vascular structure and function [8]. An association has also been reported between the time people spend seated and mortality. However, the results are even more relevant on combining the time spent seated (6 hours a day) with low physical activity (< 24.5 METS/hours/week), yielding a relative risk (RR) of 1.94 (95% confidence interval (95% CI): 1.70-2.20) for women and 1.48 (95% CI: 1.33-1.65) for males, as opposed to those who spend less time seated and have greater activity [9]. The EVIDENT study has also found increased arterial stiffness to be related to the number of hours spent watching television [10]. On the other hand, physical activity shows an inverse correlation to the concentrations of fibrinogen [11].

### Interventions for increasing physical activity

Although there is abundant evidence of the benefits of physical activity, the percentage of individuals who may be considered active is low in our setting [12]. In the United Kingdom, the prevalence of sedentarism reaches 60% in males and 74% in females [13], while in Spain the PEPAF (Experimental Program for Physical Activity Promotion) recorded a 75% sedentarism rate [14]. Different methods have been used in an attempt to promote physical activity, though with conflicting results. A Cochrane review concluded that there are no data to support the hypothesis that multiple-component community-based procedures are effective in increasing the physical activity of the population [15]. A recent metaanalysis of studies in the primary care setting has concluded that the promotion of physical activity in sedentary subjects increases the number of individuals who are classified as active subjects after 12 months (odds ratio (OR): 1.42; 95% CI: 1.17-1.73), though the effect has not been demonstrated over the long term [16,17]. The PEPAF study intervention resulted in an increase in physical activity versus the controls of 18 min./week (95% CI: 6–31 min./week), with a rise in METS/hours/week of 1.3 [95% CI: 0.4-2.2]. The proportion of individuals reaching the recommended minimum physical activity was 3.9% greater in the intervention group (1.2% to 6.9%) than in the control series. Few randomized, controlled clinical trials have evaluated the impact of interventions in terms of a decrease in sitting time, though an intervention designed to promote walking while working was able to reduce the daily sitting time by 21 minutes [18]. Evidence is even more limited in populations with chronic diseases, though an intervention in type 2 diabetics has recorded a reduction in daily sitting time of 23 minutes [19].

### Benefits of the Mediterranean diet

The Mediterranean diet is presently regarded as the model of most healthy diet. It reflects the traditional eating habits of countries such as Greece, southern Italy and Spain. The main characteristics of this diet are: a) important consumption of cereals, legumes, nuts, fruit and vegetables; b) use of olive oil for cooking purposes and for the dressing of salads and vegetables (representing the main source of fat in the form of monounsaturated fatty acids); c) moderate to high consumption of fish; d) moderate to low consumption of chicken and dairy products; e) low consumption of red meats and meat products; and f) moderate alcohol consumption, mainly in the form of red wine with meals [20]. There is convincing evidence that the Mediterranean diet may have a positive effect upon endothelial function [21] and can lower peripheral blood pressure [22]. A correlation has also been established with vascular structure, as assessed by carotid intima-media thickness [23], as well as with decreased mortality due to any cause [24] and, more specifically, due to coronary disease [25]. The results of the EVIDENT I study found obese males to show the poorest adherence [26].

### Interventions for improving eating habits (Mediterranean diet)

Few intervention studies with the Mediterranean diet have been carried out. A randomized clinical trial (the Lyon Diet Heart Study) [27], involving a modified model of the Mediterranean diet versus a control diet, concluded that the Mediterranean diet is associated with a marked reduction in cardiovascular mortality and in the incidence of cardiovascular complications among patients who have suffered myocardial infarction. However, prior to publication of the PREDIMED (Prevention with Mediterranean Diet) study [22], no randomized clinical trial had investigated whether the effects of the Mediterranean diet are superior to those of a low-fat diet in relation to the primary prevention of cardiovascular diseases. The PREDIMED study [22] was designed to determine whether the Mediterranean diet supplemented with virgin olive oil or nuts prevents the development of major cardiovascular complications in high vascular risk individuals, compared with a low-fat diet. In its initial phase, this study recorded an average increase of 1.8 points on the 14-point scale assessing adherence to the Mediterranean diet, versus an increase of 0.3 points in the control group [28]. During the first year, this implied a decrease in the prevalence of metabolic syndrome and its components and in the incidence of diabetes mellitus [28,29]. Furthermore, after four years of follow-up, the subjects in the intervention groups (Mediterranean diet) showed a 30% decrease in the incidence of major cardiovascular complications versus the control series [30].

### Evaluation of arterial aging

Aging is associated with increased arterial stiffness, which can be evaluated with different clinical and biological tools. The accepted gold standard for assessing arterial stiffness is the carotid-femoral pulse wave velocity (PWV) [31], which has been correlated to increased morbidity-mortality in both patients with cardiovascular disease and in healthy individuals [32]. Central arterial pressure has also been shown to be more strongly correlated to cardiovascular morbidity and mortality than peripheral blood pressure [33]. The central and peripheral augmentation indexes are markers of arterial stiffness which together with aortic systolic pressure and aortic pulse pressure complement the information afforded by pulse wave velocity. The cardio-ankle vascular index (CAVI) also evaluates arterial stiffness, and is able to estimate the risk of atherosclerosis and vascular age. This parameter moreover is independent of arterial pressure [34,35].

### Information technology as a support for improving health

Considering the trend in recent years in the use of mobile telephones, and the recent introduction of smartphones, it can be estimated that within 10 years, a full 80-90% of the population in developed countries will have one of these devices [36], and probably with many more applications than are available today. Information technology is finding many applications in the field of health and Medicine. Recently, short message service (SMS) communication has demonstrated its usefulness in helping people to stop smoking [37]. Smartphone applications designed to assist healthcare personnel both in training and in decision making processes in daily clinical practice and in emergency care are increasing, and there is already some evidence of their usefulness [38]. Such applications have also been used in patient care for monitoring biological parameters [39], detecting falls in the elderly [40], preventing cognitive impairment [41] and monitoring diabetes [42], as well as in cardiac rehabilitation [43] and also in the promotion of physical activity [44] and the management of [45]. Communication based on the use of mobile phones, and especially smartphones, has a strong potential to transform healthcare and clinical interventions in the community [36]. However, its effectiveness needs to be evaluated in multicenter clinical trials, as recommended by the United States Food and Drug Administration (FDA), in a way similarly to what is done with drug substances. A metaanalysis of the use of information technology in dietetic evaluation has concluded that it could improve dietary assessment in some population groups, though improved validity and reliability is required in evaluating micronutrients [46]. Many applications have been developed in the field of health, and specifically in relation to diet and exercise, destined for use by the general population. Although the acceptance and ease of use of such applications has been evaluated among young adults for the registry of eating habits and physical activity [47], they have not been tested in other population types, and little is known of their effectiveness in relation to health outcomes. Few studies have validated these tools, though some investigations are presently in course [48]. Even less work has been done to explore the impact of such applications in relation to increased physical activity and improved eating habits, and hence in terms of improvement of the health of the people who use them [49].

The present study aims to provide evidence of the effect which the new information and communication technologies, and specifically smartphone applications, could have as tools supporting changes in favor of more healthy lifestyles. An evaluation is also made of the effect of such changes upon arterial aging.

### Objectives

The first objective of this study is to develop and validate a smartphone application supporting standardized counseling to increase physical activity and adapt eating habits to the recommendations of the Mediterranean diet. The second and central objective of the study is to quantify the effect attributable to the developed smartphone application in terms of the modification of habits, adherence to the Mediterranean diet, and increased physical activity. Lastly, an evaluation is made of the effect of the modification of habits upon vascular structure and function, and therefore on arterial aging.

## Methods/Design

### Design and setting

This is a randomized, multicenter, double-blind clinical trial involving two parallel groups, designed to evaluate the possible effects of adding an information and communication tool (intervention) in support of behavioral and educational counseling (control) to promote increased physical activity and adaptation of eating habits to the Mediterranean diet.

The study will include 6 groups of the Research Network on Preventive Activities and Health Promotion (REDIAPP) in Bilbao, Cuenca, Zaragoza, Valladolid, Barcelona and Salamanca (Spain), as a continuation of the EVIDENT project developed in 2010–2012.

### Subjects

#### *Study population*

The study population will be selected from the EVIDENT project [7], comprising 1,553 subjects randomly selected in the primary care setting. The study will exclude patients over 70 years of age (due to difficulties in using information and communication tools among such individuals), those unable to do exercise or follow the Mediterranean diet, as well as those subjects who meet any of the exclusion criteria of the EVIDENT project (known coronary or cerebrovascular atherosclerotic disease; heart failure; moderate or severe chronic obstructive pulmonary disease; musculoskeletal disease that limited walking; advanced respiratory, renal, or hepatic disease; severe mental disease; treated oncological disease diagnosed in the 5 years) [7]. The rest of the subjects will be randomised on a centralized basis from Salamanca using the Epidat 4.0 software package to intervention (IG) and control groups (CG) with a ratio of 1/1. Of the 1553 subjects, it is estimated that 10-15% will be excluded; the resulting sample therefore will comprise 1,350 individuals. We estimate that another 10% will reject participation, i.e., we expect to include at least 1,215 subjects in the final sample.

#### *Sample size*

Estimation of sample size has been made for the main study endpoints. Regarding physical exercise, and assuming α = 0.05 and β = 0.10, with a standard deviation (SD) of 154, we would need 1,110 subjects (555 per group) to detect an increase of 30 counts/minute in IG versus CG. In turn, regarding the Mediterranean diet (MD), and assuming α = 0.05 and β = 0.10, with a standard deviation (SD) of 2, we would need 676 subjects (338 per group) to detect an increase of 0.5 points in the MD questionnaire in IG versus CG. The inclusion of 1,215 subjects is considered sufficient to detect clinically relevant differences in the main study endpoints, assuming the cluster effect of the design.

### Variables and measurement instruments

The general and potentially effect-modifying variables, such as age, gender, occupation, smoking, alcohol consumption, personal history and drug use will be documented.

#### *Mobile phone tool for evaluating healthy lifestyles*

The developed tool is the result of an agreement between the company CGB and the GIAPCyL research group of the REDIAPP (RD12/0005/0004), through the *Infosalud Fundation* (Figures 1 and 2). The tool is a smartphone application with a user-friendly environment that is easy for adults to handle. It can be used to quickly evaluate the adaptation of living habits to healthy lifestyle recommendations referred to both eating and physical activity. An evaluation will be made of the quantity and quality of food intake according to standardized references, with the purpose of assessing adaptation of the eating habits of the individual to the Mediterranean diet. Based on adequate proportions of primary food elements, a personalized recommendation will be produced, depending on the entered intake characteristics. The application will generate detailed information on the eating deviations (diet composition and calories), with a view to facilitating changes in habits. Physical activity also will be evaluated, using an accelerometer included in the smartphone application, and which will count the steps taken over a period of 24 hours. The activity reported by the subject during periods in which the device is not used (e.g., swimming and other sports) also will be considered, assessing compliance with the exercise objectives and providing recommendations to increase activity and reach the target of 10,000 steps a day defining an active individual. A balance of activity and diet compliance will be made at the end of the day, and specific recommendations will be produced for the next day/days. The information will be stored in the device and will be downloaded on occasion of the control visits for subsequent analysis.

**Figure 1 F1:**
[figure not shown]
**Smartphone application (APP) EVIDENT II**, **main screen and physical activity.**

**Figure 2 F2:**
[figure not shown]
Smartphone application (APP) EVIDENT II, nutrition screens.

#### *Physical activity*

Physical activity will be measured by an accelerometer and by the 7-day physical activity recall (PAR). ActiGraph GT3X accelerometers (ActiGraph, Shalimar, FL, USA) will be used to evaluate principal endpoint of psychical activity, which have been previously validated [50-52]. ActiGraph is a monitor that uses a piezoelectric acceleration sensor to filter and convert the signals produced from the sensor in samples collected at a preset frequency in hertz. The samples are summed over a user-specified time sampling interval, called an “epoch”. Output from the ActiGraph is in the form of activity “counts,” where one count is equivalent to 16 milli-g per second, and where g is equal to 9.825 m · s - 2, the acceleration of gravity. Activity “counts” are recorded to the internal memory of accelerometers by converting acceleration units over a given epoch [53]. Subjects will wear the accelerometer fastened with an elastic strap to the right side of the waist for seven consecutive days with habitual physical activity, except for bathing and performing activities in the water. All subjects will be verbally instructed on how to use the accelerometer. The accelerometer will be set to record physical activity data every minute. The MAHUFFE software, available from: http://www.mrc-epid.cam.ac.uk/research/resources/materials-transfer-disclaimer/physical-activity-downloads/ (accessed: 30/12/2013), will be used to analyze the data. Sequences of 10 or more consecutive zero counts will be considered non-wearing time and excluded from the analyses. Inclusion criteria will be a minimum of 4 days of recording, including at least 1 weekend day and at least 600 registered minutes per day. The main outcome variable from the activity monitor will be the average intensity of physical activity (counts/minute), calculated with equal weighting given to each day (regardless of registered time per day). The intensity of physical activity will be determined according to the cut-off points proposed by Freedson [54], sedentary (<100 counts/minute), light (100–1952 counts/minute), moderate (1952–5724 counts/minute) vigorous (>5724 counts/minute) and very vigorous (>9498 counts/minute). Moderate-vigorous activity will be considered as activity accumulated from all bouts lasting at least 1 min.

The 7-day PAR is a general measure of physical activity, which has been recognized as valid and reliable tool in recent years and is widely used in epidemiological, clinical and behavior change studies. It consists of a semi-structured interview (10-15 minutes) in which participants provide an estimate of the number of hours dedicated to physical or occupational activities requiring at least a moderate effort in the past seven days. The categories collected are moderate, vigorous, and very vigorous physical activity. The amount of time dedicated to each activity is multiplied by the mean metabolic equivalents (METs) of each category: light activity 1.5, moderate 4, vigorous 6, and very vigorous 10. The sum of the products of the hours dedicated to each activity and its estimated mean energy expenditure (MET) provides an estimation of the kilocalories per kilogram used per day (kcal*kg-1 * d-1). The dose of physical exercise will be estimated in METs/hour/week and active persons were considered as those doing at least 30 minutes of moderate activity, five days a week, or at least 20 minutes of vigorous activity, 3 days a week or 450 MET · min · wk^-1 ^[12]. Persons not reaching this level of physical activity were considered sedentary.

Questionnaire hours seated (Marshall): Evaluates the hours that the individual is sitting, in their work, in the displacements and at home, during the week and the weekend [55].

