### Intervention

#### *Common to both groups*

##### 

**Counseling on physical activity** Both groups (control and intervention) will receive counseling on physical activity with a view to favoring compliance with the current recommendations on physical activity in the general population. The intervention has demonstrated its effectiveness in the PEPAF study [14] and in the *Prescribe Vida Saludable* (PSV) program (Osakidetza). Counseling will consist of an individual visit lasting 15 minutes in which an explanation will be given of the health benefits of physical activity, with the recommendation to perform at least 30 minutes of moderate activity 5 days a week, or 20 minutes of vigorous activity three days a week. Counseling will be standardized in both groups, and the subjects will receive an informational brochure (Additional file 1) on the session. The first part (5 min.) will address the recommendations on physical exercise in relation to cardiovascular health. The second part (8 min.) will develop knowledge of the intensity of some specific physical activities such as walking, riding a bicycle, or other activities. The last part (2 min.) will be dedicated to answering questions and doubts. Specific advice will be given to reduce the number of hours spent sitting.

##### 

**Nutritional counseling** Both groups (control and intervention) will receive nutrition counseling aimed at favoring adherence to the MD. This intervention has been shown to be effective in the PREDIMED study [22]. Counseling will consist of an individual visit lasting 15 minutes in which the concepts of the MD will be explained, with insistence upon the importance of complying with each of the recommended points. Counseling will be standardized in both groups, and the subjects will receive an informational brochure (Additional file 1) on the session. The first part (3 min.) will develop the concept of the MD. The second part of the session (10 min.) will focus on each particular recommendation, with brief and clear messages. The last part of the interview (2 min.) will be dedicated to answering questions and doubts.

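### Treating 10 consecutive zero minutes as non-wear drops still sitting from the primary counts/minute endpoint, which can then move opposite to true activity

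*Protocol article*

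**What the plan says.** All the relevant rules stand in the protocol article under Physical activity.

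- Epoch: "The accelerometer will be set to record physical activity data every minute".
- Non-wear: "Sequences of 10 or more consecutive zero counts will be considered non-wearing time and excluded from the analyses".
- Primary activity outcome: "The main outcome variable from the activity monitor will be the average intensity of physical activity (counts/minute), calculated with equal weighting given to each day", and this holds "regardless of registered time per day".
- Valid recording: "Inclusion criteria will be a minimum of 4 days of recording, including at least 1 weekend day and at least 600 registered minutes per day".
- Intensity bands: "sedentary (<100 counts/minute), light (100–1952 counts/minute". The sedentary band includes zero.

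Under Common to both groups, the counselling on physical activity adds: "Specific advice will be given to reduce the number of hours spent sitting". Under Specific of the intervention group, the app arm is also given a target of 10,000 steps a day. Sample size plans for a difference of 30 counts/min with an SD of 154; no source is given for the SD.

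**The concern.** With one-minute epochs, ten zeros are ten minutes without registered movement. A person who wears the monitor and sits still that long is sedentary by the protocol's own cut-off, yet the minutes are handled as if the monitor had been taken off. The article gives no second criterion to separate the two.

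Two things follow. First, the primary average becomes total counts divided by minutes outside long zero-runs, so a person who replaces still sitting with gentle movement enlarges the denominator as well as the numerator. Second, the deleted minutes do not count towards the 600 registered minutes, so whether a day is valid depends partly on how still the person was. At stake is whether the objective primary endpoint ranks people, and changes within people, in the right order.

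**Working it through.** **The plan's own figure.** For a difference of 30, SD 154, two-sided α = 0.05 and power 0.90, n per arm = 2 × (1.960 + 1.282)² × 154² / 30² ≈ 554, against 555 stated. The sample size reproduces, so 30 counts/min is a fair yardstick for the changes below.

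**Replacing still sitting.** Let R be a day's registered minutes (outside zero-runs of 10 or more) and M the mean over them. Moving t minutes from a deleted zero-run to activity at L counts/min gives

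(MR + tL)/(R + t), a change of t(L − M)/(R + t).

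This is negative whenever L < M. With W worn minutes and the worn zeros kept, the change is tL/W, which is never negative. The sign condition needs no outside data; the sizes do.

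*Assumed day A* (not in the documents): 840 worn minutes, 210,000 counts, 200 minutes in zero-runs. Mean with zeros kept: 210,000/840 = 250.0. Mean under the rule: 210,000/640 = 328.1.

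| Change in behaviour | Under the rule | Zeros kept |
|---|---|---|
| 60 min at 200 | 222,000/700 = 317.1 (−11.0) | 222,000/840 = 264.3 (+14.3) |
| 60 min at 300 | 228,000/700 = 325.7 (−2.4) | +21.4 |
| 60 min at 400 | 234,000/700 = 334.3 (+6.2) | +28.6 |
| 60 min at 1,000 | 270,000/700 = 385.7 (+57.6) | +71.4 |
| 30 min at 1,952 | 268,560/670 = 400.8 (+72.7) | +69.7 |

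*Range over the baseline mean.* Assume 900 worn minutes, 200 in zero-runs (R = 700), t = 60. For M = 200, 250, 300 and 400:

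- at L = 100: −7.9, −11.8, −15.8, −23.7 (zeros kept: +6.7);
- at L = 150: −3.9, −7.9, −11.8, −19.7 (zeros kept: +10.0);
- at L = 500: +23.7, +19.7, +15.8, +7.9 (zeros kept: +33.3).

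*Range over zero-run minutes.* With 900 worn minutes, M = 250, t = 60 and L = 100, 100 zero-run minutes (R = 800) give 60 × (−150)/860 = −10.5. With 300 (R = 600) the change is 60 × (−150)/660 = −13.6.

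**Breaking up sitting.** Put one active minute at L into every ten of h formerly deleted minutes. The remaining runs are nine zeros long, no longer qualify for deletion, and re-enter the denominator. The change is

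h(0.1L − M)/(R + h), negative whenever L < 10M.

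With R = 700, M = 250, h = 120 and 12 active minutes at 2,000 counts/min (above the protocol's moderate cut-off of 1,952): (175,000 + 24,000)/820 = 242.7, a change of −7.3. With zeros kept it is 24,000/900 = +26.7. For M = 200, 300 and 400 the same behaviour gives 0, −14.6 and −29.3.

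**Validity.** A day with 900 worn minutes and 310 in zero-runs has 900 − 310 = 590 registered minutes and fails the 600-minute rule. Day A has 640 and passes.

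**The case against.** The strongest reply is that none of this shows a biased trial. The rule is the same in both arms. The advice on sitting goes to both, and the app-specific content is a step target, food entry and daily recommendations, with no mention of sitting. A reader might infer that the rule biases the primary comparison against the app. That would need the app arm to replace or break up still sitting at low intensity more than control does, and nothing in the article says it will. The step target makes a difference in sitting possible, no more. This part of the objection stands.

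The error also has no fixed direction. On day A the sign reverses only for 100 to 328 counts/min, about 12% of the light band's width (228/1,852). Sixty minutes at 1,000 counts/min keeps its sign, and 30 minutes at 1,952 is not attenuated at all. If 60 near-zero minutes outside long zero-runs were replaced by activity at 400, the rule would inflate the gain: 60 × 400/640 = +37.5 against +28.6. This stands too, although the break-up case shows that minutes above the moderate cut-off do not always protect the endpoint.

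The sizes rest on assumed days. Day A passes the 600-minute rule, and only four valid days are needed. A reader might infer that the most sedentary participants are screened out of an intention-to-treat analysis. The mechanism exists, but no loss rate or difference between arms can be derived.

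Finally, the sitting questionnaire, the 7-day recall and the moderate-to-vigorous minutes are separate measures. They would help to show an effect on sitting or activity, but they do not correct the primary average.

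**Conclusion.** The concern holds as a weakness in how the primary activity endpoint is defined. Under the stated rule, more movement can score as less, and the validity of a day depends on stillness. The sign result follows from the protocol's own rule and outcome, taking the average over the minutes that remain after exclusion. The sizes are illustrative. Sixty minutes at 100 to 150 counts/min in place of deleted sitting moves an individual's endpoint by about −4 to −24 for registered means of 200 to 400, which is 13% to 79% of the design difference of 30. These are changes within a person, not between-arm effects. Baseline means and zero-run minutes are not in the article, sustained activity above the mean still raises the endpoint, and a reversed or biased trial result is not demonstrated. Priority: should-fix, as a cheap improvement.

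**What to change.** Pre-specify a longer zero-run as non-wear (60 consecutive minutes is an example; the article offers no basis for a particular value). Use it both for the primary average and for the 600-minute rule, identically in both arms and at all visits. Report the 10-minute rule as a sensitivity analysis. Recheck that the planning SD of 154 applies under the new rule; since its source is not stated, it cannot be assumed to carry over.

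The cost is reprocessing stored minute-level data, with no new measurement. The downside is that true removals shorter than the threshold are counted as sedentary time. The protocol takes the monitor off for bathing and water activities, so short removals of that kind would enter as zeros.
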